### Plans to promote participant retention and complete follow-up

As crossover to another treatment arm than allocated is allowed, the crossover will be mentioned in the eCRF. In case of no informed consent, the patient will no longer be exposed to the allocated study intervention and the patient will be withdrawn from the study. As the eGOS assessment is recorded by a structured telephone or face-to-face interview, several attempts will be made to contact those patients not responding to the phone or not coming to scheduled visits; the general practitioner (GP) of the patient can also be contacted to facilitate outcome assessment.

### Plans for collection, laboratory evaluation, and storage of biological specimens for genetic or molecular analysis in this trial/future use

See also the “Additional consent provisions for collection and use of participant data and biological specimens” section; there will be no biological specimens collected.

### Data management.

For each randomized patient, an eCRF will be generated. Central data management will be performed using a dedicated website (https://train-esicm.clinfile.com) by the research team and data managers of the trial coordination center. Trial data will be entered in the patient’s eCRF by the local investigator or research nurse. The eCRF gives multiple tools and checkpoint to promote data quality (i.e., avoid errors in the biological variable report). The project leader will screen the website regularly for missing and incorrect data. When necessary, the project leader will contact the local investigator to adjust or complete the eCRF. The data will be kept for at least 10 years.

### Confidentiality

All randomized patients are identified by the center number followed by the patient number (i.e., 01 + 001 = 01/001). Trial personnel will not distribute patients’ names outside the local hospital. On screening forms, eCRF, and all other study documents, patients will never be identified by their names, but only by their randomization numbers. The subject identification code will be safeguarded by the local investigator.

### Statistical methods: outcomes

Analysis of data is based on intention-to-treat. Statistical analysis will be performed using the last version of SPSS for Windows (Chicago, USA). Continuous variables will be summarized using medians and quartiles and analyzed using a Wilcoxon rank sum test. Categorical variables will be analyzed using the Fisher exact test. The primary outcome comparisons will be analyzed using a chi-square analysis and reported as an absolute risk reduction of poor outcome and its corresponding 95% confidence interval. The primary outcome will also be adjusted for pre-specified covariates (stratification criteria) and presented for each category of brain injury (TBI, SAH, ICH).

All secondary outcomes will be analyzed using independent samples *t*-tests, chi-square test, as appropriate, without additional adjustment. For 28-day mortality, the Cox proportional hazard model will be used to determine time-to-event hazard ratios and 95% confidence intervals.

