## Methods: participants, interventions, and outcomes

### Study setting

This study will be conducted in 72 intensive care units (ICUs) worldwide. The complete list of recruiting sites is shown in Supplemental Table 1. The selection of participating ICUs was initiated within the Neuro-Intensive Care (NIC) Section of the European Society of Intensive Care Medicine (ESICM), with the identification of national investigators who then selected potential academic and non-academic ICUs with neurosurgical facilities and an adequate number of patients (> 50) with acute brain injury admitted per year. The study was initially expected to last 4 years, assuming the inclusion of 75–95 patients/month in 50–70 different centers. The final duration of the study will be almost 7 years, because of the slow recruitment rate, which is in part due to the recent pandemic crisis.

**Table 1 Tab1:** Inclusion and exclusion criteria of the TRAIN study

Inclusion criteria	Exclusion criteria
TBI, SAH, or ICH	Other neurological diseases, such as ischemic stroke or post-anoxic coma; status epilepticus without underlying brain injury; CNS infections (community-acquired; hospital-acquired; ventriculitis; post-operative)
Age ≥ 18 and ≤ 80 years	
GCS ≤ 13 on randomization	Known previous neurological disease, causing significant cognitive and/or motor handicap
Expected ICU stay > 72 h	ICH due to AVM or brain tumor
Hb ≤ 9 g/dL within 10 days from brain injury	Inability (religious reasons) or reduced ability (lack of compatible blood) to receive blood products
	Active and uncontrolled bleeding at the time of enrollment
	GCS of 3 with both pupils fixed and dilated; brain death or imminent death (within 24 h)
	Pregnancy
	Medical need to correct anemia (e.g., active coronary disease or severe cardiac disease) with target Hb levels > 9 g/dL
	DNE orders
	Previous allo-immunization due to transfusion, limiting RBC availability

*GCS*, Glasgow Coma Score; *ICU*, intensive care unit; *Hb*, hemoglobin; *DNE*, do-not-escalate (i.e., vasopressors, mechanical ventilation, renal replacement therapy); *CNS*, central nervous system; *ICH*, intracranial hemorrhage; *AVM*, arterio-venous malformation; *TBI*, traumatic brain injury; *SAH*, subarachnoid hemorrhage

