### Sample size

The primary outcome measure of this study is the occurrence of unfavorable neurological outcome at 180 days, evaluated by a eGOS of 1–5. To calculate the sample size, we estimated a mortality rate of 15% and a percentage of poor neurological outcome of 35% (i.e., eGOS 1–5 of 50%). There are no specific epidemiological data to support this assumption, as the population is mixed (i.e., TBI, SAH, and ICH) and the proportion of patients being eligible for the study remains unknown. Thus, the initial sample size calculation identified a total of 2095 patients needed to be recruited for each arm to achieve a power of 90% at a two-sided alpha level of 0.05 or less to detect a reduction of poor outcome rate at 180 days from 50 to 45% (absolute reduction of 5%, i.e., 10% relative reduction) in one of the two arms. Sample size calculation was adjusted twice. The first change (approved in August 2019) consisted in considering a reduction in unfavorable neurological outcome rate at 180 days from 50 to 40% (absolute reduction of 10%, i.e., 20% relative reduction, *n* = 1000) in one of the two arms, considering the relatively low number of patients being eligible for the study. The second change (approved in June 2022) consisted in considering a reduction in unfavorable neurological outcome rate at 180 days from 50 to 39% (absolute reduction of 11%, i.e., 22% relative reduction, *n* = 756–378 patients per group) in one of the two arms, with a power of 85% and at a two-sided alpha level of 0.05. Considering a potential 5% lost to follow-up, a total of 794 patients (397 per group) are needed to complete the study. This last modification was decided because of the coronavirus disease 2019 (COVID-19) pandemic, which significantly disrupted recruitment and blood availability and led to uncertainty over future recruitment.

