## Methods: assignment of interventions

### Assignment of interventions: allocation

## Sequence generation

All eligible acute brain-injured patients during the study period in one of the participating centers can be considered for enrolment in the study. Randomization is performed using a computer-generated random sequence (variable blocks of 4, 6, and 8), stratified by center, by disease (TBI, SAH, or ICH), and by the Glasgow Coma Scale (GCS) at the moment of randomization (3–5; 6–9; 10–13).

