The strengths of this study are the multicenter design of the study, the easy-to-implement protocol, the lack of additional therapeutic interventions besides standard care which will improve protocol adherence, and the inclusion of several acutely brain-injured patients (i.e., TBI, SAH, and ICH). Some limitations need also to be acknowledged. First, brain injury could occur also at higher Hb values; however, this will not be assessed in this study. Second, separation of Hb values between groups over time will not be very large [22] and one may argue that this would not be sufficient to show significant differences in outcome between the two transfusion strategies. Third, the availability of blood as well as blood storage time and quality will be dependent from local organization and participating centers.

Whether this could potentially influence the outcome of our analysis remains an unmeasured confounder, even if the outcome assessment will be adjusted to the recruiter center. Finally, the revised sample size may increase the risk to overlook a potentially clinically relevant difference in the primary outcome.

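### The deciding primary test ignores the factors that stratify randomization; making the stratification-adjusted risk difference primary would add about 0 to 5 points of power

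*Protocol article*

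**What the plan says.** All references are to the protocol article. Under Sequence generation, randomization is "stratified by center, by disease (TBI, SAH, or ICH), and by the Glasgow Coma Scale (GCS) at the moment of randomization", using "variable blocks of 4, 6, and 8". Under Study setting, "This study will be conducted in 72 intensive care units (ICUs) worldwide".

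Under Statistical methods: outcomes, "The primary outcome comparisons will be analyzed using a chi-square analysis and reported as an absolute risk reduction of poor outcome", with its 95% confidence interval. The next sentence adds a second analysis: "The primary outcome will also be adjusted for pre-specified covariates (stratification criteria"). The Discussion, on differences in local blood supply and quality, relies on center adjustment: "even if the outcome assessment will be adjusted to the recruiter center".

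The Sample size section plans for a fall in unfavorable outcome "from 50 to 39% (absolute reduction of 11%, i.e., 22% relative reduction"), "with a power of 85% and at a two-sided alpha level of 0.05". This gives 378 evaluable patients per group and 794 in total after a 5% allowance for loss to follow-up.

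**The concern.** The three factors were judged important enough to stratify on, and disease and GCS are known before allocation for every patient. The analysis that decides the trial uses none of them; the result that follows the design is placed second.

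This matters more after the sample size revisions. The target went from 2095 per arm for a 5-point difference to 794 in total for an 11-point difference, and the Discussion itself accepts a higher risk of missing a relevant effect. If disease and GCS predict outcome, adjusting for them narrows the interval without one more patient. The Discussion's reliance on center adjustment also does not apply to the test that decides.

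**Working it through.** **1. The plan's own figure.** Inputs from the Sample size section: p1 = 0.50, p2 = 0.39, difference d = 0.11, two-sided alpha 0.05 (z = 1.960), power 85% (z = 1.036), mean proportion 0.445.

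- Without continuity correction: n = [1.960 × √(2 × 0.445 × 0.555) + 1.036 × √(0.50 × 0.50 + 0.39 × 0.61)]² / 0.11² = (1.3775 + 0.7240)² / 0.0121 = 365 per group.
- With continuity correction: n' = (n/4) × [1 + √(1 + 4/(n × d))]² = 383 per group.
- The stated 378 lies between the two. Chi-square power at 378 per group: z = (0.11 × √378 − 1.3775) / 0.6985 = 1.09, so power is 86.2%.
- 756 × 1.05 = 794, as stated (756 / 0.95 would give 796).

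These are two-proportion formulas without covariates, so the size fits the chi-square. For the 10-point difference that was the target from 2019, 378 per group gives z = (0.10 × √378 − 1.3790) / 0.7000 = 0.81, or 79% power.

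**2. How thin the strata are.** 72 centers × 3 diseases × 3 GCS bands = 648 possible strata. 794 / 648 = 1.2 patients per stratum, and 794 / 72 = 11 per center. The smallest block is 4, so most blocks stay incomplete.

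**3. Power forgone.** The document does not say how strongly disease and GCS predict outcome, so a range was simulated: 2,000 trials per scenario, 756 evaluable patients, rates of 50% and 39%, and blocks of 4, 6 and 8 within center × disease × GCS. Further assumptions: TBI/SAH/ICH 60/20/20%, GCS bands 40/40/20%, unequal (lognormal) center sizes, and center standard deviation 0 to 0.6 on the logit scale. The Monte Carlo standard error of each power figure is about 0.7 points.

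| Assumed c-statistic of disease + GCS | Chi-square | Adjusted for disease + GCS | Difference (points) |
|---|---|---|---|
| 0.50 (not prognostic) | 87.2% | 87.1% | −0.1 |
| 0.61 | 86.9% | 87.8% | +0.9 |
| 0.66 | 88.1% | 90.4% | +2.3 |
| 0.70 | 86.5% | 90.8% | +4.3 |
| 0.77 | 89.1% | 93.8% | +4.7 |

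**4. Validity and scale.** In two null scenarios (c about 0.66 and 0.70) the chi-square rejected in 5.1% and 4.1% of trials, and the model with disease and GCS in 5.7% and 4.3%. The standardized risk difference from that model averaged −0.110 to −0.111 against a true −0.110, so the stated effect measure is kept.

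**5. How center enters.**
- Stratifying the estimate over every center × disease × GCS cell (Mantel-Haenszel) is close to unbiased. However, only about 518 of 756 patients fall in cells containing both arms, and the spread of the estimate is 14 to 25% larger than for the unadjusted difference (0.0376/0.0329 = 1.14; 0.0443/0.0354 = 1.25).
- Center dummies in a linear risk-difference model left the estimate at about −0.110 to −0.111.
- Center dummies in an ordinary maximum-likelihood logistic model moved the log odds ratio about 10–11% away from zero (for example −0.557 against a true −0.501), with null rejection of 7.1% and 5.8%.

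**The case against.** The case for leaving the plan alone is substantial. The chi-square is simple, valid and the test for which the sample was computed. The adjusted analysis is already planned in the next sentence, in a clear order. The gain depends on a prognostic strength that no figure in the document supports; the Sample size section says there are no specific epidemiological data even for the overall event rate. The change would also come late: Trial status reports 791 recruited, the trial is open-label, and an interim analysis had already looked at the main outcome.

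Most of this stands, and it limits the point to efficiency and ordering. It does not answer why the analysis that follows the randomization should be the secondary one, since adjustment cost almost nothing when the factors were not prognostic. The planned adjustment does deal with chance imbalance, but only in a result that does not decide. The late date is a reason to document the change properly. Data collection was planned to run to June 2023, so there was time before the final analysis.

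A reader might also infer that the planned adjustment would bias the result because 72 centers would enter as dummies. The document does not support that. It names no logistic model, no dummies and no odds ratio. Its stated measure is an absolute risk reduction, on which no material bias appeared. How center enters the model may properly be left to the statistical analysis plan.

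**Conclusion.** The point holds as one of efficiency and of matching the analysis to the design. The forgone power is about 0 to 5 points at 756 evaluable patients. This rests on assumed c-statistics of 0.50 to 0.77 and on the assumed case mix and center sizes. The power figures are for adjustment for disease and GCS; a random intercept for center was not simulated.

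A reader might infer that the chi-square is invalid or that the trial falls short of its planned power. Neither follows: its simulated type I error is 4.1–5.1%, and the stated sample size delivers the planned 85% with that test. This should be changed if it can be done before the final analysis, but the trial's conclusion would not be unsound without it.

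**What to change.** Before the final analysis, name one primary analysis: a logistic model with treatment, disease and GCS stratum, from which the standardized absolute risk difference and its 95% confidence interval are reported. State the method for the interval. Use the GCS bands of the randomization (3–5, 6–9, 10–13), not the different bands listed for the subgroup analysis. Handle center by a random intercept or by pooling small centers under a rule fixed in advance; do not stratify over all 648 cells. Keep the chi-square as a supportive analysis.

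If an odds ratio is also reported, it should not come from an ordinary maximum-likelihood logistic model with 72 center dummies. This is a precaution, since the protocol does not state such a model.

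Cost: modest dependence on the model and a dated amendment, made by people who have not seen outcomes by group. No new data are needed, because the stratification factors are recorded at randomization.

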## Methods: data collection and management

### Plans for assessment and collection of outcomes

Data collection on admission will include the following: demographic characteristics, comorbidities, source of admission, primary and secondary admission diagnoses, Acute Physiologic Assessment and Chronic Health Evaluation (APACHE) II score (the worst values of the first 24 h), Sequential Organ Failure Assessment (SOFA) score on admission, GCS immediately after injury, GCS on hospital admission after initial resuscitation, initial Hb concentration, and sodium and glucose levels.

For patients with TBI, the following data are also collected: Marshall score on cerebral CT scan (the worst of the first 24 h), presence of traumatic SAH and/or epidural mass on CT scan, pupillary reactivity, mechanisms of injury, hypoxemia (defined as a SpO_2_ < 90% for more than 5 min with or without endotracheal intubation and under oxygen therapy) and/or hypotension (defined as a systolic blood pressure < 90 mmHg for more than 5 min despite fluid resuscitation) before or on hospital arrival, intracranial pressure (ICP) monitoring within the first 48 h, and previous therapy with antiplatelet drugs or anticoagulants.

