For patients with SAH, the following data are also collected: World Federation of Neurological Society (WFNS) score; Fisher CT-scan scale; ICP monitoring within the first 48 h; pupillary reactivity on arrival; hydrocephalus; diagnosis of vasospasm (either using trans-cranial Doppler [TCD], contrast CT scan, and/or angiography); development of delayed neurological ischemic deficit (DNID); therapies for DNID; and occurrence of DCI. TCD-vasospasm is defined as a mean flow velocity in any vessel > 200 cm/s or > 120 cm/s and a Lindegaard ratio > 3 [22]. Angiographic or contrast CT-scan vasospasm is defined by a neuroradiologist as moderate-to-severe arterial narrowing (> 50%) on specific imaging not attributable to atherosclerosis, catheter-induced spasm, or vessel hypoplasia. Definition of DNID is based on the development of new focal neurological signs, deterioration in the level of consciousness, or both, when the cause is felt to be ischemia attributable to vasospasm after other possible causes of worsening (e.g., hydrocephalus, seizures, metabolic derangement, infection, or excessive sedation) have been excluded [23]; as such, DCI is defined as the appearance of DNID and/or a new infarction on cerebral CT scan or magnetic resonance imaging (MRI), when the cause was attributed to vasospasm [23].

For patients with ICH, the following data are collected: ICH volume > 30 mL on the initial CT scan (measured/estimated by local neuroradiologist); the presence of intra-ventricular hemorrhage; location (deep, cortical, infratentorial); ICP monitoring within the first 48 h; and pupillary reactivity on arrival.

Daily data collection (only during the ICU stay) includes daily GCS score; Hb concentration (minimum and maximum); sodium and glucose levels at 8 am (or the first value of the day); ICP levels at 8 am (or the first value of the day); maximum ICP levels during the day; SOFA score; the presence of infection (location, pathogen, treatment); the presence of sepsis; the occurrence of serious adverse events (*see paragraph on adverse events*); the need for second-tier therapies for increased ICP (hypothermia; barbiturates; decompressive craniectomy) or seizures (convulsive or non-convulsive); and daily fluid intake and urine output (to calculate daily fluid balance).

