### Statistical methods: additional analyses

Subgroup analyses will be performed according to (a) underlying brain injury (TBI vs. SAH vs. ICH); (b) GCS at the moment of randomization (3–5; 6–8; 9–11); (c) presence of increased intracranial hypertension (defined as the need for specific therapies to reduce intracranial pressure [ICP]—if no ICP monitoring, then the patient is considered as not having intracranial hypertension); (d) age (< 45 years or ≥ 45 years); and (e) SOFA on randomization (< 8 and ≥ 8). Post hoc analyses will include (a) high- vs. middle- to low-income countries and (b) high-recruiting (i.e., > 25 patients) centers vs. others. All analyses will be processed by an independent statistician.

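### The adjusted analysis of the primary outcome uses only the stratification criteria and leaves out age and pupillary reactivity: valid and unbiased, but a modest amount of precision is given up

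*Protocol article*

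**What the plan says.** Under Statistical methods: outcomes, the headline comparison is unadjusted: "The primary outcome comparisons will be analyzed using a chi-square analysis and reported as an absolute risk reduction of poor outcome", with a 95% confidence interval. A second analysis follows: "The primary outcome will also be adjusted for pre-specified covariates (stratification criteria) and presented for each category of brain injury (TBI, SAH, ICH"). The first parenthesis closes the covariate list. Under Sequence generation, randomization is "stratified by center, by disease (TBI, SAH, or ICH), and by the Glasgow Coma Scale (GCS) at the moment of randomization (3–5; 6–9; 10–13"). The only other remark on adjustment, in the Discussion, concerns the recruiting center.

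Two baseline variables outside that list are available across the trial population:

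- **Age.** It is an eligibility criterion in Table 1 ("Age ≥ 18 and ≤ 80 years"), so it is known for everyone. The data collection section also covers it: "Data collection on admission will include the following: demographic characteristics, comorbidities, source of admission". Statistical methods: additional analyses uses it as a subgroup factor: "d) age (< 45 years or ≥ 45 years").
- **Pupillary reactivity.** Plans for assessment and collection of outcomes lists it for TBI (no time point given), for SAH (on arrival) and for ICH: "ICP monitoring within the first 48 h; and pupillary reactivity on arrival".

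Neither is a stratification factor.

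**The concern.** If age or pupillary status predicts the 180-day outcome, a model that omits them leaves outcome variance unexplained that the trial's own data could explain. It also corrects a chance difference between arms in these variables only as far as they correlate with center, disease and GCS.

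Two features of this trial make that worth attention. The sample size was cut twice, and the Discussion accepts that the revised size may miss a clinically relevant difference; using baseline data already collected costs no patients. Balance on the stratification factors is itself likely to be weak: 72 × 3 × 3 = 648 cells for 794 patients is about 1.2 per cell, with blocks of 4, 6 and 8.

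**Working it through.** **1. The plan's own figure.** Inputs from Sample size: 50% vs 39%, two-sided alpha 0.05, power 85%, 378 evaluable per arm, 397 after 5% loss.

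n = [1.960·√(2·0.445·0.555) + 1.036·√(0.25 + 0.2379)]² / 0.11² = (1.3775 + 0.7240)² / 0.0121 = 365 per arm, or 383 with continuity correction. At 378 per arm, power = Φ[(0.11·√378 − 1.3775)/0.6985] = Φ(1.09) = 86.2%. The stated 378 lies between the two versions, and 756 × 1.05 gives 794. The figure is accepted.

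The 95% CI half-width without covariates is 1.96·√(0.4879/378) = 7.0 percentage points.

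**2. Chance imbalance at 397 per arm.** The SD of the standardized age difference is √(2/397) = 0.071. The probability of a difference above 0.1 SD is about 16%, and above 0.15 SD about 3.5%. For abnormal pupils at an assumed prevalence of 10%, 20% or 30%, the probability of a difference above 5 percentage points is about 2%, 8% or 12%.

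Effect of a 0.1 SD age imbalance on the risk difference, approximated by ln(OR) × 0.1 × 0.445 × 0.555:

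- OR 1.25 per SD (assumed): 0.223 × 0.0247 = 0.6 points.
- OR 1.75 per SD (assumed): 0.560 × 0.0247 = 1.4 points.

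**3. Gain over the planned model.** The right contrast is strata-only against strata + age + pupils. It was simulated with 1,500 trials of 756 patients per scenario, using a linear risk-difference model with robust standard errors. Assumptions:

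- marginal risks of 50% and 39%;
- three equal disease groups and three equal GCS classes, with arms balanced within disease by GCS;
- odds ratio of 2 between adjacent GCS classes;
- abnormal pupils in 35%, 17% and 8% of the GCS classes, lowest to highest;
- centers not modelled.

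| Assumed OR: age per SD / abnormal pupils | Power, strata only | Power, + age + pupils | Mean SE |
|---|---|---|---|
| 1 / 1 | 89.5% | 89.3% | 0.0344 → 0.0345 |
| 1.25 / 1.5 | 88.7% | 89.2% | 0.0343 → 0.0340 |
| 1.5 / 2 | 87.3% | 89.3% | 0.0342 → 0.0334 |
| 1.75 / 3 | 88.1% | 91.6% | 0.0342 → 0.0326 |

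The simulated gains are 0.5, 2.0 and 3.5 points where the covariates are prognostic. The SE falls by about 1%, 2% and 5%.

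**4. Cross-check.** Each simulated power has a Monte Carlo error of about √(0.89·0.11/1500) = 0.8 points. Putting the mean SEs into Φ(0.11/SE − 1.96) gives 89.4% → 89.9%, 89.6% → 90.9% and 89.6% → 92.1%, which are gains of 0.5, 1.3 and 2.6 points. The order of magnitude holds, and 3.5 is the upper end of the range.

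**5. Sparseness of center.** 756/72 = 10.5 evaluable patients per site on average, so fixed center terms would be thin with or without the extra covariates.

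**The case against.** The strongest case against is that nothing here is wrong. Adjusting for pre-specified stratification factors is a recognized and unbiased choice, ordinary chance imbalance is already covered by the confidence interval, and other covariate sets are a matter of preference. The adjusted analysis is also the supporting one, so new covariates there cannot raise the power of the chi-square test. All of this stands, and it limits the point to the efficiency and robustness of the adjusted estimate.

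The evidence for prognosis is also thin in the document itself. An age subgroup concerns effect modification, not prognosis, and no section ranks pupils as a predictor. Pupils are recorded on arrival in SAH and ICH and without a time point in TBI, whereas anemia may arise up to 10 days after injury. Patients with a GCS of 3 and both pupils fixed and dilated are excluded. A collection list does not guarantee complete data. These objections stand as reasons to treat prognostic strength as an assumption and to call the expected gain small. They do not remove the point, because including the variables costs essentially no power if they turn out not to matter.

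A reader might infer a much larger loss. With the variance multiplied by (1 − R²), power at 378 per arm rises from 86.2% to 89.5% at R² = 0.10, 92.7% at 0.20 and 94.1% at 0.25. That calculation starts from no covariates at all, although disease, GCS and center are already in the planned model, and the document gives no basis for 20% or 25% of added explained variance.

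**Conclusion.** The point holds as a modest weakness of the adjusted analysis. The covariate set is closed at center, disease and GCS, while age (known for all) and pupillary reactivity (collected in all three diagnoses) go unused. Under assumed odds ratios of 1.25 to 1.75 per SD of age and 1.5 to 3 for abnormal pupils, adding them gains about 0.5 to 3.5 power points over the planned model. With no prognostic effect the difference is negligible (89.5% vs 89.3%).

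The document does not support reading this as bias, as an invalid primary analysis or as an underpowered primary test. Protection against imbalance is reduced, not absent, since GCS, disease and center remain in the model. The Discussion's caution about missing a relevant difference concerns the sample size and should not be attributed to the covariate choice.

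**What to change.** Before analysis by arm, state that the adjusted model for the primary outcome contains:

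- disease and GCS class at randomization, as planned;
- center, handled in a way that tolerates about 10 patients per site, for example as a random effect;
- age as a continuous term;
- pupillary reactivity on arrival where recorded, with a missing category.

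Report the standardized absolute risk difference from this model with its 95% CI beside the chi-square result, which stays as planned.

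The main outcome was already reported to the monitoring committee by coded group at the 300-patient interim analysis. The choice should therefore be fixed and dated by those who have not seen outcomes by group.

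The cost is a sentence or two of analysis wording, a rule for missing pupil data and slightly more analysis work. Data collection, sample size and patient care do not change.

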### Study outcomes

The primary outcome measure is the proportion of patients with unfavorable neurological outcome at 180 days after randomization, assessed using the eGOS and dichotomized as “unfavorable” (eGOS 1–5) or “favorable” (eGOS 6–8). This scale has been largely used to assess neurological outcome in different interventional randomized trials dealing with acute brain-injured patients; mortality is part of the scale (eGOS 1).

Secondary outcome measures are (1) 28-day survival; (2) eGOS distribution between the two groups (i.e., ordinal outcome analysis); (3) ICU and hospital lengths of stay; (4) presence and severity of extra-cerebral organ dysfunction/failure, assessed using the daily Sequential Organ Failure Assessment (SOFA) score; (5) infection rate, except those involving only the central nervous system (CNS); (6) composite outcome (death and/or organ dysfunction/failure); (7) fluid balance; and (8) for centers monitoring brain tissue oxygenation (PbtO_2_), time spent with P_bt_O_2_ < 20 mmHg (brain hypoxic burden) will also be collected and analyzed, but reported into a separate secondary analysis.

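### The SOFA severity comparison is fixed as unadjusted although SOFA at randomization is available: a valid test, but one that gives up precision and leaves a realised baseline imbalance uncorrected

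*Protocol article*

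**What the plan says.** Secondary outcome 4 in *Study outcomes* is "presence and severity of extra-cerebral organ dysfunction/failure, assessed using the daily Sequential Organ Failure Assessment (SOFA) score". Outcome 6, "composite outcome (death and/or organ dysfunction/failure", also draws on organ failure.

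*Statistical methods: outcomes* states for these and the other secondary outcomes: "All secondary outcomes will be analyzed using independent samples *t*-tests, chi-square test, as appropriate, without additional adjustment". Earlier in the same section a general rule reads: "Continuous variables will be summarized using medians and quartiles and analyzed using a Wilcoxon rank sum test". Covariate adjustment is planned in one place only: "The primary outcome will also be adjusted for pre-specified covariates (stratification criteria"). Cox regression is named for 28-day mortality.

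A baseline SOFA exists. *Plans for assessment and collection of outcomes* lists SOFA on admission and again among the data recorded each day in the ICU. *Statistical methods: additional analyses* uses "SOFA on randomization (< 8 and ≥ 8") as a subgroup factor. Randomization is "stratified by center, by disease (TBI, SAH, or ICH), and by the Glasgow Coma Scale (GCS) at the moment of randomization" (*Sequence generation*), so SOFA is not among the strata.

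**The concern.** When an outcome is a later reading of a score that was also taken at baseline, the baseline value is usually one of its best predictors. Patients may be enrolled up to 10 days after the injury, so organ function at randomization can differ a good deal between patients, and part of that difference will persist. Adjusting for it costs no patients and no new data.

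The article does not leave the matter open. It states a no-adjustment rule, gives no reason, and does plan adjustment for the primary outcome. Organ dysfunction is also a natural place to look for the fewer complications that *Objectives* expects under the restrictive strategy. At stake are a wider interval than necessary and, if the arms happen to differ in SOFA at entry, an organ-failure result that carries part of that difference.

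**Working it through.** **Inputs.** From *Sample size*: 50% vs 39%, 85% power, two-sided 0.05, 378 per group, 397 per group after 5% loss. From *Trial design*: 1:1 allocation. Assumed: the correlation rho between SOFA at randomization and a continuous SOFA summary, taken as 0.3, 0.5 and 0.7.

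**1. The plan's own figure.** No figure is given for SOFA, so the n comes from the primary outcome.

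- Without continuity correction: n = [1.960·√(2·0.445·0.555) + 1.036·√(0.25 + 0.2379)]² / 0.11² = 365 per group.
- With continuity correction: 383 per group. The stated 378 lies between the two, and power at 378 is 86.2%.
- Allowance for loss: 378 × 1.05 = 397, as stated.

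So 378 per arm is a usable basis.

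**2. Unadjusted comparison of a continuous SOFA summary (SD = 1).**

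- SE = √(2/378) = 0.0727 SD.
- Difference detectable with 80% power = (1.960 + 0.842) × 0.0727 = 0.204 SD.

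**3. With baseline SOFA as a covariate.** The variance is multiplied by 1 − rho². Power at 0.204 SD is Φ(0.204 / [0.0727·√(1 − rho²)] − 1.960), and the detectable difference is 0.204·√(1 − rho²).

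| rho | variance factor | SE reduction | power at 0.204 SD | detectable difference | patients the unadjusted test needs for equal precision |
|---|---|---|---|---|---|
| 0.3 | 0.91 | 5% | 84% | 0.194 SD | × 1.10 |
| 0.5 | 0.75 | 13% | 90% | 0.176 SD | × 1.33 |
| 0.7 | 0.51 | 29% | 97.5% | 0.146 SD | × 1.96 |

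The 5% loss concerns the 180-day outcome, so 397 per arm may be nearer for SOFA. Then 0.199 SD falls to 0.190, 0.172 or 0.142 SD, and the powers are the same.

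**4. Chance imbalance.** The difference in mean baseline SOFA has SE 0.0727 SD.

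- 95% of randomizations fall within ±0.14 SD. An imbalance above 0.1 SD has probability 17%, and above 0.2 SD 0.6%.
- An imbalance of 0.1 SD moves the unadjusted difference by 0.1·rho, that is 0.03 to 0.07 SD, or 0.4 to 1.0 of its SE.
- Given an imbalance of k SE and no treatment effect, the unadjusted z statistic is normal with mean k·rho and variance 1 − rho². At k = 1.96 (0.14 SD) the rejection rate is 7.9%, 12.9% or 20.5% for rho 0.3, 0.5 or 0.7.

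The rates in the last item hold only for a trial at that edge. Averaged over all randomizations the rate is 5%.

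**The case against.** **The unadjusted comparison is valid.** This stands. Randomization balances SOFA in expectation, and the stated error rate and interval already allow for chance imbalance. A reader might infer that the planned test is biased, that its type I error is inflated, or that nothing in the design balances SOFA. The documents support none of these. The conditional rates above describe an unlucky trial, not expected performance. Stratifying by center, disease and GCS may also balance some of the severity mix, although GCS does not directly balance the extra-cerebral components.

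**The SOFA summary is not defined.** This also stands. The outcome has a presence part, which is binary, and a severity part; the article does not say whether severity is a maximum, a mean or a change. The figures apply only to a continuous summary. If that summary were change from baseline, the baseline would already enter. With equal SDs, however, a change score has variance factor 2(1 − rho), that is 1.4, 1.0 and 0.6 at rho 0.3, 0.5 and 0.7, against 0.91, 0.75 and 0.51 for covariate adjustment. The choice of summary may properly be left to a fuller document.

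**Rho is assumed.** True, and at 0.3 the gain is modest. If the outcome omits the neurological component and the baseline score includes it, the correlation could be lower.

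**Availability is partly inferred.** SOFA on randomization is named only as a subgroup factor. That use and the daily ICU recording make it very likely available, but the article does not say that the value precedes treatment.

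**Other readings of the rule.** The adjustment ruled out might be for multiplicity, or the Wilcoxon rule might govern. Neither brings a covariate in. Nor does the SOFA subgroup analysis, which asks whether the effect differs by baseline and does not adjust the overall comparison.

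**Conclusion.** The point holds as a matter of efficiency, not validity. The article states an unadjusted rule for a severity outcome that has its own baseline measurement, and no section brings that measurement into the comparison. For a continuous summary with 378 per arm, the cost is the difference between 80% power and 84% to 97.5%, or between a detectable 0.204 SD and 0.194 to 0.146 SD, over an assumed rho of 0.3 to 0.7. A chance imbalance, if one occurs, also stays in the estimate.

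The size rests on the assumed rho, on a continuous summary, and on an n taken from the primary outcome. The figures do not extend to the binary presence part. A secondary outcome is affected; the primary result is not. The change is worth making because it is nearly free, not because the planned test would mislead on average.

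**What to change.** For the continuous SOFA severity outcome, replace the unadjusted test with a linear model containing treatment and SOFA at randomization as a continuous covariate. Define the covariate as a pre-treatment value and, where possible, build it from the same extra-cerebral components as the outcome. Fix this before unblinding and report the unadjusted comparison as supporting.

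A mixed model over days should not be offered as an interchangeable alternative. Daily SOFA is recorded only during the ICU stay, so the series ends at death or ICU discharge. Such a model would need its own assumptions about the unobserved days, and baseline adjustment does not resolve that problem in either model.

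The cost is a sentence or two of analysis wording. No new data should be needed, since the subgroup analysis already requires SOFA at randomization. What has to be confirmed is that the recorded value precedes treatment.
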